#### Intervention component three: individualized dietary education

To enhance capability, individual education on how to make dietary changes will be provided on the same visit as the physical activity education. The research assistant will provide education on food items which contains high sodium content from the participant’s usual diet, education on reduction of salt consumption and high salt spices, finding alternative options for food with lower sodium content (for example brown bread instead of white bread), limiting cooking salt to one teaspoon per day, and removing salt from the table during meals. Opportunity for consuming healthier food items will be enhanced by encouraging habitual consumption of self-grown vegetables and naturally growing wild herbs which participants already have access to in their communities. Participants will be motivated through weekly monitoring calls where they will be asked to list which dietary adjustments they achieved weekly. The research assistant will keep record of everyone’s weekly dietary habits so that feedback and motivation can be enhanced during weekly telephone feedback.

The authors are cognizance of the under-pinning theories that influence behaviour change such as the social cognitive theory [33]. The primary variable of interest in this theory of motivation is self-efficacy, which concerns someone’s belief in his/her capabilities to successfully execute necessary courses of action to satisfy situational demands [33, 34]. According to Bandura [34], a high expectation of self-efficacy and outcome expectancy leads to greater adherence to a recommended activity (in our case, physical activity and diet adaptations). Alongside the COM-B model, we developed taxonomies of behaviour change techniques (BCTs) (Tables 1, 2 and 3) to identify active intervention ingredients and allow for future replication [35, 36]. The BCTs are classified using the Behaviour Change Taxonomy [36].

The scope and sequence of the intervention are provided in Table 4. The intervention will run over a period of 10 weeks. During week 0, baseline individual assessments of blood pressure, body mass index, waist-hip ratio, and urine sample collection will be conducted. Participants will be asked to wear a wrist-worn accelerometer for seven consecutive days. They will also be asked to complete a 24-h diet recall questionnaire. During week 1, participants will be invited to a group education session limited to up to 10 participants per group. Participants will be asked to return the accelerometer device during the group session. The research assistants will note down the recruitment rate, intervention uptake, and any reasons for refusal to take up the intervention. Week 2 of the intervention will consist of individual household visits to provide participants with physical activity and diet education based on set goals and to provide printed pamphlet of the education components. The research assistants will telephone the participants weekly for monitoring support and motivation. On week 10, the research assistants will conduct household visits and reassess all baseline measurements. Participants will be asked to wear the acceleromer for 7 days as a post-intervention measure. Adherence rate, completion rate, follow-up rate, and fidelity will be assessed. An exit interview will be conducted to assess intervention acceptability.

**Table 4 Tab4:** Scope and sequence of the intervention

Programme components	Sequence			
	**Week 0**	**Week 1**	**Week 2 (household visit)**	**Week 10 (household visit)**
**Group educational programme**		Group education sessions		
**Individualized physical activity**			• Goal setting • Physical activity intervention education • Provide printed intervention pamphlet	Final data collection of self-monitoring physical activity tool
**Individualized diet**			• Goal setting • Dietary intervention education • Provide printed intervention pamphlet	Final data collection of self-monitoring physical activity tool
**Anthropometric measurements**	Baseline individual assessment • Demographic data • Blood pressure • BMI^a^ • WHR^a^ • Urine sample collection			Follow-up individual assessment • Blood pressure • BMI^a^ • WHR^a^ • Urine sample collection
**Physical activity assessment**	Baseline accelerometer wear for 7 days	Return accelerometer		Follow up accelerometer wear for 7 days (collect after 7 days)
**Dietary assessment**	Nutrition questionnaire—24-h diet recall			Follow up nutrition questionnaire- 24HR diet recall
**Feasibility parameters**		• Recruitment rate • Intervention uptake and engagement • Reasons for refusal		• Adherence rate • Completion rate • Follow-up rate • Acceptability interview • Fidelity

^a^*WHR* waist-hip ratio

^a^*BMI* body mass index

### Self-monitoring support

Due to reported low literacy levels in the HAALSI cohort [26, 37], self-monitoring support which does not require the participants to read or write will be provided. The trained research assistants will telephone each participant once weekly to ask questions about the participant’s identified physical activity and dietary goals. The research assistant will have a copy of each participant’s printed intervention and record progress. Participants will be asked to provide personal and alternative contact number. Where a participant cannot to be reached via telephone, a household visit will be conducted. The self-monitoring support is also noted as an active behaviour change technique due to its ability to enhance motivation of adhering to an intervention [35].

### Outcomes and criteria for success

In line with the primary objective (c) of the study, the criteria adapted for judging the feasibility of progressing to a larger-scale evaluation (Table 5) were initially developed by Avery and colleagues’ [38] top Ten tips for guiding the decision to progress from a pilot to a definitive trial and later reproduced by Hynes and colleague [39]. The criteria were also discussed by the study authors guided by existing literature.

**Table 5 Tab5:** HYPHEN progression criteria

HYPHEN progression criteria	Go—proceed to larger scale (RCT)	Amend—proceed with changes	Stop—do not proceed unless changes possible
Feasibility of participant recruitment—can 30 participants be recruited in 1 week?	If 30 participants are recruited in 1 week (100%)	If 15 to 29 participants are recruited in 1 week (50 to < 100%)	If < 15 participants are recruited in 1 week (< 50%)
Feasibility of patient retention—can at least 80% of recruited participants be retained until study end?	≥ 24 (80%) retained	21–24 (70–80%) retained	< 21 (70%) retained
Feasibility of engagement—can at least 80% of recruited participants provide complete weekly data	≥ 24 (80%) engaged	21–24 (70–80%) engaged	< 21 (70%) engaged
Feasibility of intervention implementation	Delivery of intervention judged strongly feasible by qualitative data	Delivery of intervention judged feasible by qualitative data	Delivery of intervention judged possibly feasible by qualitative data

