### Sample size

A study which provides guidance on conducting feasibility studies by Tickle-Degnen [27] states that feasibility studies are not expected to have large sample sizes as they do not need to power statistical null hypothesis testing. However, Arian and colleagues [28] in their review of current best practice state that the sample size of feasibility studies should be adequate to estimate critical parameters such as recruitment rate. An overall sample size of 30 has been recommended by Lancaster, Dodd, and Williamson [29]. We will aim to recruit 30 participants at the beginning of the intervention.

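### Table 5 places 24 of 30 (80%) in both Go and Amend for retention and engagement, and its fixed counts match their percentages only if the final number recruited is 30

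*Protocol article*

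**What the plan says.** The protocol article, under Outcomes and criteria for success, gives the progression criteria in Table 5. Primary feasibility outcome measures then names that table as the way primary objective (c) is assessed.

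- **Retention.** The row asks: "can at least 80% of recruited participants be retained until study end". Go is "≥ 24 (80%) retained", Amend is "21–24 (70–80%) retained" and Stop is "< 21 (70%) retained".
- **Engagement.** The row asks: "can at least 80% of recruited participants provide complete weekly data". It uses the same three pairs of count and percentage; its Amend cell reads "21–24 (70–80%) engaged".
- **Recruitment.** This row concerns recruitment within one week. Its Amend cell, "If 15 to 29 participants are recruited in 1 week (50 to < 100" per cent), stops short of the Go value in both count and percentage.

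The Sample size section says: "We will aim to recruit 30 participants at the beginning of the intervention". No text says which band 24 belongs to, whether count or percentage governs when they differ, or whether recruitment goes on after the first week.

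**The concern.** There are two separate faults.

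First, the Go and Amend cells share an endpoint. A result of 24 out of 30 satisfies both, in two of the three numeric rows. This needs no shortfall and no assumption about recruitment: it occurs at the planned size.

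Second, the row questions set a proportion of those recruited, while the cells set fixed counts. The two agree exactly only if 30 people are recruited, and 30 is an aim.

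No hypothesis test decides progression here, so these thresholds are the quantitative decision rule for objective (c). A rule that gives two labels to one result leaves the label to be settled once the result is known, which is what prespecified criteria are meant to avoid.

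**Working it through.** **Inputs.** Target recruited: 30 (Sample size). Thresholds: 80% and 70% of those recruited, printed as 24 and 21 (Table 5, retention and engagement rows).

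**Reproducing the plan's figures.** 0.80 × 30 = 24 and 0.70 × 30 = 21. Both are exact, so the counts are right for 30.

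**Overlap at 30.** 24/30 = 80.0%. The Go cell (24 or more) includes it, and so does the Amend cell (21 to 24). No other count carries two labels.

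**How often 24 would occur.** The document gives no expected retention or engagement rate, so I assume a true rate p between 70% and 90% and independent participants. Then P(X = 24) = C(30,24) × p^24 × (1 − p)^6. At p = 0.80 this is 593,775 × 0.004722 × 0.000064 = 0.179.

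| Assumed p | P(exactly 24 of 30) |
|---|---|
| 0.70 | 0.083 |
| 0.75 | 0.145 |
| 0.80 | 0.179 |
| 0.85 | 0.137 |
| 0.90 | 0.047 |

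**Count against percentage at other final numbers N.** By percentage, Go needs the smallest whole number at or above 0.8N, and Amend the smallest at or above 0.7N (exactly 80% is taken as Go, following the row question). By count, the printed cut-points stay at 24 and 21 whatever N is.

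| N | Go from (by %) | Amend from (by %) | Examples where the band differs |
|---|---|---|---|
| 30 | 24 | 21 | none, apart from the double label on 24 |
| 29 | 23.2, so 24 | 20.3, so 21 | none, apart from the double label on 24 |
| 28 | 22.4, so 23 | 19.6, so 20 | 23 (82.1%): Go by %, Amend by count; 20 (71.4%): Amend by %, Stop by count |
| 26 | 20.8, so 21 | 18.2, so 19 | 21 (80.8%): Go by %, Amend by count |
| 25 | 20 | 17.5, so 18 | 20 (80.0%): Go by %, Stop by count |
| 23 | 18.4, so 19 | 16.1, so 17 | 23 (100%): Go by %, Amend by count |
| 20 | 16 | 14 | 20 (100%): Go by %, Stop by count |

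A Go by percentage that is a Stop by count requires the percentage threshold for Go to be 20 or less: 0.8N ≤ 20, so N ≤ 25. At N = 26 the threshold is 21, which is Amend by count, so 25 is the largest N with a Go/Stop conflict. At N = 21 to 23 nobody can reach 24, so Go by count is impossible. At N of 20 or fewer, even complete retention is below 21 and is Stop by count.

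**The case against.** The strongest reply is that the table nearly settles the matter itself. Both row questions ask about at least 80%, and 24 of 30 is at least 80%. The Go cell says so too, and the recruitment row shows that exclusive bands were intended. On that reading, 24 in the Amend cells is a slip for 23. Likewise the denominator is stated in the row questions, and the counts read naturally as the illustration for 30. This is the likeliest intention, and it limits the harm. It does not remove the fault, because the Amend cells still contain 24 and 80%, and no sentence ranks count and percentage.

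A second reply concerns consequences. At 30 the only ambiguity is Go against Amend, at one count, and both labels allow progression. Even Stop is qualified by the possibility of changes. That stands, and it lowers the importance of the point.

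A reader might infer more: that the recruitment row permits this study to run with 15 to 29 people, so that any shortfall yields conflicting verdicts. The document does not support that. The row measures what is achieved in one week, and its column headings concern the larger trial. With 20 recruited in the first week and 30 in total, the counts 24 and 21 are exact. Nor does every final shortfall cause a conflict: 29 moves no result between bands, and a Go/Stop conflict needs 25 or fewer.

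**Conclusion.** The concern holds in two parts of unequal strength.

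1. **Unconditional.** For retention and for engagement, 24 of 30 is both Go and Amend. Under an assumed true rate of 70% to 90%, each row has about a 5% to 18% chance of landing there. The peak of 18% applies only if the true rate is 80%.
2. **Conditional.** If the final number recruited is below 30, and if the counts are taken to govern, count and percentage give different bands for some results at 28 or fewer. They can give Go and Stop for the same result at 25 or fewer, and the count rule gives Stop even at 100% at 20 or fewer. Whether this arises depends on recruitment that the document leaves open.

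The thresholds are wrong as written and belong to a primary objective, but the importance is moderate. No estimate or analysis is affected, and at the planned size the ambiguity is between two labels that both lead on. It would be going too far to say that the team will pick the more favourable label; the table merely leaves room for it.

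**What to change.** Define the retention and engagement rows by percentage of participants actually recruited, in bands that do not overlap and that keep the authors' cut-points:

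- Go: 80% or more.
- Amend: 70% or more but less than 80%.
- Stop: less than 70%.

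Show counts only as the illustration for 30 recruited: 24 or more, 21 to 23, and 20 or fewer. State that the percentage governs if the final number differs. At 25 recruited the same rule gives 20 or more, 18 to 19, and 17 or fewer, so every result falls in exactly one band.

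The cost is rewording two table rows, preferably before results are seen. No data collection, sample size or analysis changes.

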#### Primary feasibility outcome measures

For primary objective a of the study, nine focus-group discussions were conducted as part of the needs analysis process, and the outcome is presented in Tables 1, 2 and 3. For primary objective b of the study, we followed a model of behaviour change as outlined in Fig. 1, and the outcomes are presented in Tables 1, 2 and 3. Primary objective c will be assessed as per Table 5.

The feasibility study parameters which will be used to inform the design of a larger HYPHEN intervention trial are outlined in Table 4. Demographic data (age, sex, employment status, type of employment) of participants who refuse to participate in the intervention will be recorded as well as their reasons for refusal. Acceptability of the intervention will be assessed using an in-depth semi-structured interviews through a self-developed interview guide. All participants who were recruited will be invited for the interviews including those who did not complete the intervention. The interview topics and questions will focus on predetermined themes of participants’ perceived expectations of the intervention, benefits, motivations, and barriers. These topics will be explored in relation to participants age, sex, and employment status. Participants will also be asked to rate their overall satisfaction with the intervention using a Likert scale [40]. Fidelity of intervention delivery will be assessed by the primary author to ascertain whether the field workers provided the intervention as intended using a checklist framed around the intended BCTs (Table 6).

**Table 6 Tab6:** Fidelity of delivery of intervention

**Definition** [41]	**Intervention BCTs**	**Example**
**Intervention is delivered as intended**	Information about antecedents	Facilitator provided education on all identified aspects of physical activity and diet
	Goal setting	Facilitator identified and made a tick of the participant’s goals for physical activity and diet modifications
	Instruction on how to perform a behaviour	Facilitator explained to the participant how to perform identified goals with images on a printed handout
	Self-monitoring of behaviour	Facilitator followed with each participant weekly and noted with a tick based on participant’s responses
	Avoidance/reducing exposure to cues for the behaviour	Facilitator explained with pictures to the participant how to identify and avoid/replace food items with lower sodium salt

#### Secondary outcome measures

Secondary outcomes which will be assessed are outlined in Table 7 and are as follows: (i) Blood pressure will be measured using a oscillometry blood pressure monitor, (ii) body mass index will be measured using a stadiometer and a portable LED weighing scale, (iii) waist-hip ratio will be measured using a rubber tape measure, (iv) urinary sodium will be measured by collecting participants urine sample, (v) physical activity will be measured using an Axivity AX3 wearable device on the wrist, and (vi) diet will be assessed using a 24-h diet recall questionnaire.

**Table 7 Tab7:** Secondary outcome measure outline

Variable	Tool used	Manufacturer	Participant position/instruction	Procedure
**Blood pressure**	Oscillometry blood pressure monitor	OMRON M3 comfort, Japan	Sitting on a chair with back supported with feet on the ground. Cuff wrapped on upper arm	Three measurements recorded and the average of the last two will be calculated [42]
**Body mass index**	Portable stadiometer	SECA, Germany	Standing on the scale with shoes off, no cap or hat worn on head	Body mass index will be calculated by dividing the participant’s weight in kilograms by the participant’s height in metres squared [43]
	Portable LED weighing scale	DQUIP, India	Standing on the scale. Shoes off, no heavy clothing worn, no items in pockets	
**Waist-hip ratio**	Rubber tape measure (centimetres)	N/a	Waist: participant standing shoulder width apart, measuring around participant’s waist at the smallest point Hip: participant standing shoulder width apart, measuring around participant’s hip at the widest part	Waist circumference divided by hip circumference [44]
**Urinary sodium**	Urine sample	N/a	N/a	On-the-spot urine sample collected in a 300-ml container and stored at temperatures of − 80 °C in a laboratory upright biomedical freezer. Samples will be analysed in a clinical laboratory which adheres to good clinical laboratory practice (GCLP) standards. Samples will be tested only for sodium levels
**Physical activity**	Axivity AX3	Axivity Ltd., UK	Participant to wear the axivity wristwatch and instructed not to remove it	Device worn on the nondominant wrist with an adjustable watch strap over 7 full days consecutively
**Diet**	24-h diet questionnaire	[45]	Participant asked to recall all food consumed in the past 24 h	Record type of food consumed for breakfast, lunch, dinner, and any snack meals

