**Methods:**

We aim to recruit 30 adult participants with a self-report hypertension diagnosis. A one-arm, prospective design will be used to assess the feasibility and acceptability of recruitment, uptake, engagement, and completion of the 10-week intervention. Recruitment rates will be assessed at week 0. Intervention uptake, engagement, and adherence to the intervention will be assessed weekly via telephone. Blood pressure, body mass index, waist-hip ratio, urinary sodium, accelerometer-measured physical activity, and 24-h diet recall will be assessed at baseline and at 10 weeks. Qualitative semi-structured interviews will be conducted at 10 weeks to explore feasibility and acceptability.

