### Data and statistical analysis

#### Quantitative analysis

A Consolidated Standards of Reporting Trials (CONSORT) flowchart will be used to present the flow of participants throughout the intervention. The CONSORT flowchart will also present reasons for declining participation or withdrawing. Descriptive statistics will be used to present baseline statistics and outcomes of feasibility. Depending on data distribution, mean and standard deviation or median and interquartile range will be described. Pre- and post-intervention outcome change will be assessed using a paired *t*-test if data is evenly distributed. If data is unevenly distributed, the Wilcoxon signed-rank test will be used. Confidence interval is set at 95%.

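### Spot urine tested for sodium alone cannot separate a change in salt intake from a change in urine dilution

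*Protocol article*

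**What the plan says.** In the protocol article, Table 7 (Secondary outcome measures) describes the urinary sodium measure as an "On-the-spot urine sample collected in a 300-ml container", frozen and sent to a clinical laboratory, and adds "Samples will be tested only for sodium levels". Table 4 schedules one collection at week 0 and one at week 10. No timed collection or urine volume is described.

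Salt reduction is the main content of the dietary component. Intervention component three includes "limiting cooking salt to one teaspoon per day, and removing salt from the table during meals".

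Under Aim and objectives, urine sodium is a secondary indicator to be described before and after the intervention. The feasibility of the evaluation measures falls under the third primary objective. Quantitative analysis goes beyond description: "Pre- and post-intervention outcome change will be assessed using a paired" t-test, or a Wilcoxon signed-rank test if the distribution requires it. Study design states that there is one arm.

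**The concern.** A urine sodium concentration depends on how much sodium was excreted and on how much water it was dissolved in. The usual way to allow for the second is to measure a dilution marker in the same sample. Here the text does not merely leave a marker unmentioned: the word restricting the assay to sodium rules one out. A fuller protocol consistent with the article would not fill the gap.

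A fall in spot sodium at week 10 could mean that participants ate less salt, drank more, or gave the sample at a different time of day. The reverse can also happen, with a real reduction hidden by more concentrated urine. The paired test and its 95% interval reflect random variation only, so they would not reveal either problem. What is at stake is the interpretation of the one biochemical measure of the main dietary target, and what the study can say about using that measure in a larger trial.

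**Working it through.** The protocol gives no expected change, standard deviation or power figure for urinary sodium, so there is no figure to reproduce. The volumes and standard deviations below are assumptions, shown as ranges.

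**Inputs from the protocol article**
- One spot sample per visit, sodium the only analyte (Table 7).
- Two visits, week 0 and week 10 (Table 4).
- Target of 30 participants (Sample size); retention thresholds of 24 and 21 (Table 5).
- Paired t-test or Wilcoxon test, 95% interval (Quantitative analysis).

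**Step 1. Effect of dilution**

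Concentration = sodium excreted / urine volume. The relative change in concentration is (1 + change in sodium) / (1 + change in volume) − 1.

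| Assumed change in volume | Sodium unchanged | Sodium truly 20% lower |
|---|---|---|
| −30% | 1/0.7 − 1 = +43% | 0.8/0.7 − 1 = +14% |
| −20% | 1/0.8 − 1 = +25% | 0.8/0.8 − 1 = 0% |
| 0% | 0% | −20% |
| +20% | 1/1.2 − 1 = −17% | 0.8/1.2 − 1 = −33% |
| +30% | 1/1.3 − 1 = −23% | 0.8/1.3 − 1 = −38% |

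Dilution can create an apparent fall, exaggerate a real one, or cancel it.

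**Step 2. Random and systematic shifts**

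On the log scale, mean change in concentration = mean change in log sodium − mean change in log volume. If volume varies at random between visits, the second mean is near zero and only noise is added. If volume shifts in one direction for the group, the second mean is a bias that does not shrink with sample size. With one arm there is no second group in which to see it.

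**Step 3. How noisy the measure may be**

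The assumed within-person standard deviation of log concentration per occasion is s = 0.3, 0.5 or 0.7. The paired difference then has standard deviation √2 × s. The test is two-sided at 0.05, with power from the noncentral t distribution.

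| n | Smallest fall detectable with 80% power (s = 0.3 / 0.5 / 0.7) | Power for a true 20% fall (s = 0.3 / 0.5 / 0.7) |
|---|---|---|
| 30 | 20% / 31% / 41% | 80% / 39% / 22% |
| 24 | 22% / 34% / 45% | 69% / 32% / 18% |
| 21 | 24% / 37% / 47% | 63% / 28% / 16% |

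With small variation and stable dilution, a group fall of 20 to 30% could be seen. With larger variation it probably could not.

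**Step 4. What a dilution marker does**

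(sodium / volume) / (creatinine / volume) = sodium / creatinine. Volume cancels. The ratio still varies with day-to-day intake, and it assumes that each person's creatinine excretion is similar at the two visits.

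**Step 5. Number of samples**

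30 × 2 = 60 at most; with 24 retained, 30 + 24 = 54.

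**The case against.** The strongest defence is that the protocol never undertakes to estimate salt intake or sodium excretion. Urine sodium is a descriptive secondary indicator, Sample size disclaims powered hypothesis testing, and none of the four progression criteria in Table 5 uses it. Random differences in hydration add noise and do not move the group mean; a spurious group change needs a systematic shift, and nothing in the documents shows that one will occur. The weekly calls also record which dietary adjustments participants say they achieved, so salt behaviour is not observed through urine alone.

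Most of this stands, and it limits the importance of the point without removing it. A before-after change is to be tested, salt is what the dietary education targets, and the weekly reports are self-reported with no baseline. A systematic shift cannot be ruled out, and the data as planned could not show whether one had happened.

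A reader might go further and infer that neither dietary measure can show a change in salt intake, because the 24-hour recall captures nothing but the type of food. The documents do not support that. The recall procedure in Table 7 is "Record type of food consumed for breakfast, lunch, dinner, and any snack meals", with no word restricting it to type, and the participant instruction is "Participant asked to recall all food consumed in the past 24 h". The cell condenses a cited questionnaire that is not shown and may record portions and added salt. How a diet variable would be scored for a paired test is commonly left to the analysis plan. Food type alone can also show switches that the education teaches, such as brown bread for white. For urine, saying that it cannot show a change is too absolute, as step 3 of the working shows.

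**Conclusion.** The point holds for the urine measure. As specified, a week 0 to week 10 change in spot sodium concentration cannot be attributed to salt intake, because the only analyte does not allow dilution to be separated out and the one-arm design offers no comparison. Under assumed volume changes of 20 to 30% in either direction, the distortion for one person runs from −23% to +43% with no change in sodium at all. The group mean is distorted only as far as such shifts run in a common direction, and the documents give no figure for that. Uncorrected spot sodium remains a confounded, noisy indicator and not an empty one.

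The diet recall is not a finding; at most it calls for a confirmation. The article gives no clock times for urine collection, which field procedures may well fix, so that silence is not a fault either. This is a worthwhile, cheap improvement to a secondary outcome. It changes no progression decision.

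**What to change.** - Assay creatinine as well as sodium on the same stored samples, at most 60, and amend the sodium-only statement in Table 7.
- Analyse the paired change in the sodium-to-creatinine ratio, and report raw sodium concentration alongside.
- Collect each participant's two samples at a similar time of day and record the time.
- If creatinine cannot be added, report the result as spot sodium concentration and state that it is not interpreted as a change in salt intake.
- As a request only: confirm that the cited recall questionnaire records amounts and added salt.

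The cost is one small additional assay per sample and some care in scheduling the week 10 visit. Because the text limits testing to sodium, the consent and ethics wording must be checked first, and an ethics amendment may be needed. That is easiest to arrange before samples are collected.
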